#### Setting and recruitment

The research participants will be recruited from the health visiting teams employed by the local community NHS trust. Participants will be purposefully recruited to include health visitors and their wider teams who are about to deliver a universal home visit to families of children aged 9–12 months—the target age group for the HABIT intervention.

The health visiting leads (SG & VS) for this project will identify health visitors and their wider teams who deliver regular universal home visits to parents of children aged 9–12 months according to the inclusion/exclusion criteria described below. The identified health visitors and their wider teams will be emailed through their local senior manager, with the covering letter, participant information sheet and consent form. Interested participants will be contacted by the NHS trust Clinical Studies Officer, who will explain the study and obtain written consent.

#### Sample size

Six health visitors will be involved in the study in order to assess variation in that role. Although much of the assessment will be qualitative, there will be sufficient data to estimate an intra-class correlation coefficient (ICC) and confidence intervals. This ICC estimate is likely to be imprecise and will need to be supported by other similar or future studies.

#### Type of participants

The following inclusion and exclusion criteria will be adopted:

*Inclusion criteria*:Health visitors/wider members of health visiting teams who are about to deliver a universal home visit to parents of children aged 9–12 months in the local community

*Exclusion criteria*:Health visitors/wider members of health visiting teams who infrequently deliver universal home visit at 9–12 months age

#### Data collection

Diaries will be sent out to the recruited health visitors’ work email addresses. Diaries will be set up with password protection, thus enabling the health visitor to securely return the diary to the HABIT research team once they have populated their thoughts. It will take around 5–7 min to complete the diary.

The focus group will be conducted at a time and place most convenient for all six recruited health visitors and wider members of health visiting teams. The focus group will be preferably arranged during office hours and in a convenient location. The focus group will be recorded using a digital sound recorder and will last 60–75 min.

#### Data analysis

Diary and focus group data will be analysed using framework analysis based on Ayala et al. definition of acceptability [35] and Gray-Burrows et al.’s [28] model for intervention mapping to develop a home-based parental-supervised toothbrushing intervention for young children. Transcripts will be coded using an inductive approach, and thematic analysis [36, 37] will be carried out. The data will be managed with the computer software programme QSR NVivo 10.

### Acceptability of the HABIT resources for parents

#### Design of the study

This part of the study will use mixed methods to test acceptability of the HABIT resources for parents of children aged 9–12 months. Prior to the mandatory 9–12-month Child Health Review by the HABIT-trained health visitor, the HABIT research team will visit parents who have consented to take part in the study and collect baseline PSB data. Parents will then receive a home visit by the trained health visitor who will use the HABIT resource package for parents. At 2 weeks and 3 months following the HABIT intervention, the research team will undertake further home-based data collection around effectiveness of current toothbrushing, duration and parent/children (dyad) interaction during toothbrushing, and toothbrushing activity. This will enable changes in PSB practices and attitudes to be monitored. Home-based qualitative semi-structured interviews with parents will then be undertaken to explore deeper and wider structures behind barriers and facilitators that influence parents’ behaviour, and acceptability of the provided intervention and HABIT resources for parents.

#### Setting and recruitment

The research participants will be recruited purposefully from the health visiting 9–12-month waiting list. The sample will be recruited to involve parents of children aged 9–12 months living within the local community with a range of different socio-economic and ethnic minority groups. A total of 30 parents will be recruited.

Suitable parents will be identified by a Clinical Systems Specialist with the Health Visiting team who will run a report for each of the six recruited, HABIT-trained, health visitors. The report will identify the next 20 families that are due to receive a 9–12-month home visit for each of the six HABIT-trained health visitors. An invitation letter, participant information sheet and consent form will accompany a reminder notice that is normally posted to parents prior to the home visit. Participants will continue to be recruited until five parents of each of the six recruited health visitors consent to take part in the study. If a parent withdraws from the study before the health visitors attend the focus group, a new parent will be recruited and will undergo the same research process as other participants. However, if a parent decides to stop participation after the focus group with health visitors has taken place, new parents will not be recruited. Interested parents will be consented by the NHS trust Clinical Studies Officer. Recruitment will be restricted to parents of children aged 9–12 months due to the nature of the HABIT resources that specifically target this age group.

#### Sample size

The sample size of 30 participants (e.g. five parents from each of the six HABIT-trained health visitors) will be selected so that the key parameters for a trial could be determined including acceptability of the HABIT resources, exploration of intervention mechanism and acceptability of data collection in the home setting.

#### Type of participants

The following inclusion and exclusion criteria will be adopted:

*Inclusion criteria*:Parents of children aged 9–12 months who are about to receive a universal home visit by the HABIT-trained health visitorParents of children age 9–12 months who live in the local communityParents who meet the above inclusion criteria and whose children have at least one erupted tooth

*Exclusion criteria*:The opposite of those described above

#### Data collection

Data will be collected about the following variables: sociodemographic characteristics, effectiveness of current toothbrushing, duration and parent/child interaction during toothbrushing, toothbrushing activity, self-reported toothbrushing and dietary behaviours, acceptability of the HABIT intervention and qualitative enquiry to explore mechanism of action.

Data collection with parents will consist of at least three rounds:First round—*Baseline data collection*. In the home setting, baseline PSB data will be collected before the universal home visit provided by the HABIT-trained health visitor. A researcher will ask validated questions of parents about their PSB habits, e.g. self-reported PSB [24] including questions about brushing frequency, use of fluoride toothpaste, parental involvement, and age of initiation. Three different proxy objective measures of PSB will be collected:Effectiveness of current toothbrushing—children pre-brushing plaque levels on the buccal surface of each erupted primary tooth will be quantified using an established index [38];Duration and parent/child (dyad) interaction during toothbrushing—the researcher will film the dyad toothbrushing and this will be subsequently evaluated by the HABIT research team using an established PSB index [39];Toothbrushing activity—parents will be provided with a regular children toothbrush in conjunction with a Magic Timer app for their phone/tablet which monitors frequency and duration of children brushing. Magic Timer app is freely available on the Internet for members of the public. For parents who do not have or are unable to use devices providing access to the app, a hard copy of the Magic Timer diary with aspects of the Magic Timer app will be provided.

For measuring plaque level, a food colouring agent will be used and then wiped away. In cases where children are allergic to a food colouring agent or parents refuse these to be used, pre-brushing plaque levels will not be measured. The activity will be carried out either at the parent’s home setting or a health care setting where they normally see a health visitor. The baseline data collection will approximately take 30–45 min.

Plaque level data and filmed materials will be accessible only for the HABIT research team and any of the information that could identify them or a child will not be available outside the HABIT research team. Only the videos for which parents provide written consent to be used for training purposes will be used by the HABIT research team when delivering training for health visitors or for other professional activities.

Sociodemographic data will be collect about parents’ ethnicity, education, employment status and experience, and family finances. We will also collect dietary data on type and frequency of foods and drinks parents give to their children on everyday basis, breastfeeding, bedtime routine, and drinking and dummy/thumb sucking practices [40].

*Intervention delivery*. Dyads (parent/child) will then receive their home visit where the HABIT intervention will be delivered by the trained health visitor as part of their mandatory 9–12-month Healthy Child review.2.Second round*—2-week data collection*. At 2 weeks following the intervention delivered by the trained health visitor, further self-reported and objective measures of PSB (see a-c) and self-reported dietary data will be collected following the protocols identified.3.Third round—*3-month data collection*. Identically to the second round, at 3 months after the intervention, further self-reported and objective measures of PSB (see a-c) and self-reported dietary data will be collected following the protocols identified. This measurement schedule is shaped by the time taken for habits to become established [41], e.g. PSB adoption.4.Fourth round—*qualitative interviews*. Parents who took part in one or more rounds of the study will be invited to attend a qualitative interview. A topic guide will be used as the framework for the discussion and will shape the conversation around the experience of receiving oral health advice by the trained health visitor, the HABIT information package for parents and their usability in everyday child toothbrushing practices, strengths and weakness of the resources and potential behaviour changes after the intervention. The parents will be also invited to discuss acceptability of the data collection procedures and assessment. Qualitative face-to-face interviews will provide deeper and broader insight into how cultural, interactional, contextual and situational factors shape parents’ position toward and experiences of child oral health and toothbrushing as well as enabling us to detect and link social structures and processes that affect these positions and experiences [42]. The topic guide has been developed based on Ayala et al.’s [35] definition of acceptability and Gray-Burrows et al.’s [28] model for intervention mapping to develop a home-based parental-supervised toothbrushing intervention for young children. The two frameworks will enable the exploration of the acceptability of the HABIT resources as well as key barriers and facilitators (e.g. knowledge, skills, confidence and attitudes) which may influence parents’ experience and intentions to use the resources and initiate behaviour change. The interviews will take place either in the parent’s home or a public location convenient to a participant such as a café or a coffee shop where they feel comfortable talking about their infant’s oral health. The interview will last approximately 45–60 min and will be digitally recorded and professionally transcribed after the event. The recording will be deleted after accuracy of the transcription and recording is checked. All identifying information will be removed from the transcripts to ensure anonymity.

#### Data analysis

This study will produce three objective measures (a-c) which aim to quantify the underlying latent concept of PSB. These will be combined with a ‘measurement model’ (see Fig. 1) as it is referred within the structural equation modelling literature. It is anticipated that as the quality of PSB increases, the three objective measures will increase. The latent variable PSB will capture those components which co-vary. That is, PSB will quantify the covariance of the objective measures.

**Fig. 1 Fig1:**
[figure not shown]
The measurement model

Since PSB will be captured at three different times (0, 2 and 12 weeks), a growth model (see Fig. 2) can be fitted with a baseline value and a slope value.

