### Aims of study

This study, through working with health visitors and parents of children aged 9–12 months, aims (i) to explore the acceptability of the HABIT intervention to health visitors and parents of children, (ii) to examine the mechanism of action of the HABIT intervention on PSB adoption and maintenance and (iii) to develop a suitable objective measure(s) of PSB adoption.

Using a mixed-methods approach, it will specifically:Explore how the HABIT oral health intervention works in practice and how it influences behaviour changeIdentify intervention mechanisms that are most likely to lead to the adoption of PSB within the daily routineEstablish the acceptability of the HABIT oral health intervention to parents and health visitorsDevelop and correlate different objective measures of toothbrushing with parental self-reports of PSB

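### One baseline and one slope over 0, 2 and 12 weeks cannot tell an early gain that is held from one that fades or one that comes late

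*Protocol article*

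**What the plan says.** The Data analysis section for parents combines three objective measures into a latent PSB variable. It then says that, with PSB captured at 0, 2 and 12 weeks, "a growth model (see Fig. 2) can be fitted with a baseline value and a slope value". It mentions no second slope, change point, freely estimated time score or separate 2-week contrast. Fig. 2 is cited for the model but is not available here.

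The rounds sit around one intervention visit. Under Data collection, "baseline PSB data will be collected before the universal home visit provided by the HABIT-trained health visitor". Under Design of the study for parents, "At 2 weeks and 3 months following the HABIT intervention, the research team will undertake further home-based data collection".

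The second aim is "to examine the mechanism of action of the HABIT intervention on PSB adoption and maintenance". The Discussion adds that the study will evaluate whether, and in what way, HABIT changes oral health behaviour. On timing, Data collection says "This measurement schedule is shaped by the time taken for habits to become established".

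**The concern.** Three rounds give three means. A baseline and a linear slope describe them with two parameters, so the model imposes a constant change per week. Of any change over 12 weeks, 2/12 = 1/6 must then fall before week 2 and 10/12 = 5/6 after it.

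Because HABIT is delivered once, between baseline and the 2-week round, a step by week 2 is one pattern the analysis should be able to show. So are a step that is later lost and a gain that appears only after week 2. These have different meanings for adoption and maintenance, and a single slope merges them. At stake is the reported change in PSB, which is meant to inform the design of the definitive trial.

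**Working it through.** **Inputs.** The times 0, 2 and 12 weeks and the two parameters come from the parents' Data analysis section. The article gives no slope, effect size or residual variance, so there is no stated figure to reproduce. Assumptions: time scores equal to the stated weeks and equal residual variances at the three rounds. A random intercept, with or without a random slope, leaves the weights below unchanged, and so does the number of dyads.

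**Slope weights.** With complete data the slope is the sum of (t − mean t)·y / Sxx.
- Mean t = (0 + 2 + 12)/3 = 4.667.
- Sxx = 4.667² + 2.667² + 7.333² = 82.67.
- Weights per week: −4.667/82.67 = −0.0565 at baseline, −2.667/82.67 = −0.0323 at week 2, +7.333/82.67 = +0.0887 at week 12.

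**Results by pattern.** The true means are relative to baseline. The modelled 12-week change is 12 × slope, and the fitted baseline is mean y − 4.667 × slope.

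| True means at 0, 2, 12 weeks | Slope per week | Modelled 12-week change | Fitted baseline |
|---|---|---|---|
| Early and held: 0, d, d | 0.0565d | 0.68d | 0.40d |
| Steady: 0, d/6, d | 0.0833d | 1.00d | 0 |
| Late: 0, 0, d | 0.0887d | 1.06d | −0.08d |
| Early, half lost: 0, d, d/2 | 0.0121d | 0.15d | 0.44d |
| Early, all lost: 0, d, 0 | −0.0323d | −0.39d | 0.48d |

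The first three rows share the same true 12-week gain, yet the modelled change runs from 0.68d to 1.06d. In the first row the modelled 2-week gain is 2 × 0.0565d = 0.11d, where the true gain is d. An early gain that is fully held also has the same slope as steady growth to only 0.68d, so the slope does not identify the pattern.

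**When the slope turns negative.** For means 0, d, f·d the slope is (−0.0323 + 0.0887f)d. It is zero at f = 2.667/7.333 = 0.364. The slope is therefore negative once more than about 64% of the early gain is lost.

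**Sensitivity.**
- Last round at 13 weeks: the 2-week weight is −0.0306.
- Baseline taken 1 or 4 weeks before the visit: −0.025 or −0.010.
- Residuals autocorrelated in time: the weight stays negative and shrinks towards zero.
- Unequal residual variances: with precision weights w, the 2-week weight is positive only if 2 exceeds the weighted mean time, that is 2·w₀ > 10·w₁₂. This needs a 12-week residual variance more than 5 times the baseline one.
- Equally spaced scores 0, 1, 2: the slope weights are −0.5, 0 and +0.5. The 2-week mean then has no influence on the slope, which still cannot separate the patterns.

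**The case against.** The strongest reply is that the article never says the slope is linear and gives no time scores. In structural equation modelling the loadings would normally appear in the diagram, and Fig. 2 is not available here. A growth model with one free time score also has one baseline and one slope, and it would largely remove the problem. This stands as a condition on the finding. It does not dispose of it, because the text describes no such freedom.

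Three further points stand in part.
- The aims attach no time windows to adoption or maintenance, and the stated reason for the schedule fits adoption building up over the whole period. A reader might infer that adoption means weeks 0 to 2 and that a jump by week 2 is the expected pattern. The article says neither. The point needs only that the pattern is unknown beforehand.
- The Abstract assigns mechanism of action to brief exploration at home visits and to 20–25 qualitative interviews, so the slope is not the sole evidence for that aim. It remains the only quantitative description of change.
- The model is worded as something that can be fitted, in a single-group study of 30 dyads. The measures are ranked by standardised factor loadings, and nothing stops round-by-round values from being reported.

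A reader might also infer that the model treats dyads as independent although they are nested in six health visitors. That would rest on silence. The health visitors' Sample size section says "there will be sufficient data to estimate an intra-class correlation coefficient (ICC) and confidence intervals", and cluster terms are the kind of detail a condensed article leaves out.

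**Conclusion.** The point holds for the model as worded, on three assumptions: no free time score in Fig. 2, time scores of 0, 2 and 12, and a 12-week residual variance not above about 5 times the baseline one. A single slope then cannot distinguish an early gain that is held, an early gain that fades and a late gain. For the same 12-week gain it reports about two thirds of the true change in the first case and slightly more than the true change in the last.

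The negative 2-week weight might suggest that early adoption always lowers the estimated effect, or that any fading gives a negative slope. Neither follows. The first is true only when the baseline and 12-week values are held fixed, and a maintained early gain still gives a positive slope. The second needs most of the gain to be lost: the half-lost case remains positive.

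The consequence is limited to the reported change in PSB and its reading for adoption and maintenance. The choice of objective measure does not depend on the slope. This should be fixed before analysis, but it does not threaten the study's main outputs.

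**What to change.** Keep the latent PSB measurement model and let its mean be free at each round: round as a categorical factor, a piecewise mean with a step between the first two rounds, or a free time score. The free time score is the weakest of these if PSB returns to its baseline mean by 12 weeks. The slope mean is then zero, and the model cannot show a 2-week gain.

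Report three changes, each with a confidence interval: 2 weeks minus baseline, 3 months minus 2 weeks, and 3 months minus baseline. If Fig. 2 already frees a time score, say so in the text and add these changes.

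The cost is analysis wording and one extra mean parameter, with slightly less precision if change is truly linear. No new data or visits are needed, and the latent variable need not be replaced by separate models for each measure.

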**Fig. 2 Fig2:**
[figure not shown]
The growth model

Factor loadings will be available from the measurement model. By generating a standardised model where the variance of each objective measure is scaled to unity, the associate standardised factor loadings will effectively rank the measures according to the strength of their contributions to PSB. These will be taken as the quantitative assessment for each measure.

The qualitative data will be analysed in a similar way to that described earlier. The decision as to the most appropriate measure to use in a future trial will draw upon both quantitative and qualitative evidence and will be pragmatic.

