## Conclusions

This early phase study will ensure the support for PSB is suitable for health visitors to deliver and acceptable to parents. It will identify the most appropriate objective measure/s of PSB. It will enable an estimate of intra-class correlation coefficient (ICC) and confidence intervals for designing the definitive trial. The results will be used to design a larger study to test whether the PSB intervention can prevent decay (effectiveness) and save the NHS money.

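### Loadings from 30 families are used to rank the three objective measures with no allowance for sampling error, and the Conclusions promise identification without the caveat given to the ICC

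*Protocol article*

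**What the plan says.** In the protocol article, the Data analysis section for parents sets up a one-factor measurement model: "This study will produce three objective measures (a-c) which aim to quantify the underlying latent concept of PSB". The measures are plaque level, the filmed brushing index and brushing activity, taken at three visits: "Since PSB will be captured at three different times (0, 2 and 12 weeks), a growth model" can be fitted. After standardising, "the associate standardised factor loadings will effectively rank the measures according to the strength of their contributions to PSB". The next sentence fixes their role: "These will be taken as the quantitative assessment for each measure". No standard error, interval or rule for close values is mentioned. The section closes by saying that the choice of measure for a future trial "will draw upon both quantitative and qualitative evidence and will be pragmatic".

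The number of families is set in the parents' Sample size section: "The sample size of 30 participants (e.g. five parents from each of the six HABIT-trained health visitors"). The reason given is that "key parameters for a trial could be determined including acceptability of the HABIT resources, exploration of intervention mechanism and acceptability of data collection". Separating the three measures is not among the stated purposes, although developing an objective measure is the third aim under Aims of study.

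The Conclusions say of the study: "It will identify the most appropriate objective measure/s of PSB". The ICC is handled differently. The health visitors' Sample size section plans confidence intervals for it, warns that it will probably be imprecise, and says it will need support from other studies.

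**The concern.** The plan commits to reading an order off three point estimates from 30 families. If sampling error is as large as the gaps between the true loadings, the order can easily change from one sample of families to the next. The definitive trial would then receive, as its quantitative evidence on the outcome measure, a ranking that looks settled and is not. A measure could be marked down although it is the better one. The people making the pragmatic choice could not tell whether the quantitative evidence should outweigh the qualitative evidence or give way to it. The article recognises this kind of limit for the ICC but not for the loadings, which come from the same families.

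**Working it through.** **Inputs from the article.** 5 parents × 6 health visitors = 30 families; three indicators; three occasions; ranking by standardised loading. The article states no precision or probability for the ranking, so there is no figure of its own to reproduce.

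**Assumptions.** The true loadings are not in the article. Ten sets were tried. The indicators are taken as normal, the one-factor model as correct and families as independent. For pooled rounds, loadings are equal over time, with between-visit correlations of 0.3–0.9 for the factor and 0.1–0.8 for the unique parts.

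**Formula.** With three indicators the model is just identified, so λ₁ = √(r₁₂·r₁₃/r₂₃), and likewise for the others. It follows that λ₁/λ₂ = r₁₃/r₂₃. Measure 1 ranks first exactly when r₂₃ is the smallest of the three correlations.

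**Hand check, true loadings 0.8/0.7/0.6, one round.**
- Implied correlations: r₁₂ = 0.8×0.7 = 0.56; r₁₃ = 0.8×0.6 = 0.48; r₂₃ = 0.7×0.6 = 0.42.
- Measure 1 beats measure 2 only if the sample r₁₃ exceeds r₂₃. The true gap is 0.06.
- Standard errors, (1−r²)/√29: 0.7696/5.385 = 0.143 for r₁₃ and 0.8236/5.385 = 0.153 for r₂₃.
- The two share an indicator. Their covariance term is r₁₂(1−r₁₃²−r₂₃²) − ½r₁₃r₂₃(1−r₁₂²−r₁₃²−r₂₃²) = 0.56×0.5932 − 0.1008×0.2796 = 0.304.
- SD of the difference: √[(0.7696² + 0.8236² − 2×0.304)/29] = √(0.6626/29) = 0.151.
- Chance that the top two are in the right order: Φ(0.06/0.151) = Φ(0.40), about 65%. Measure 1 must also beat measure 3, so the chance of first place is lower still; simulation gives 59%.

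**Simulation, n = 30: chance that the truly best measure ranks first (33% if all three were equal).**

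| Assumed loadings | One round | Three rounds pooled |
|---|---|---|
| 0.7/0.65/0.6 | 44% | 51%* |
| 0.6/0.5/0.4 | 45% | 53%* |
| 0.7/0.6/0.5 | 51% | 52–62% |
| 0.7/0.5/0.3 | 56% | 58–67% |
| 0.8/0.7/0.6 | 59% | 62–73% |
| 0.8/0.6/0.4 | 64% | 67–76% |
| 0.8/0.5/0.5 | 66% | 71–85% |
| 0.9/0.6/0.3 | 69% | 71–81% |
| 0.9/0.7/0.5 | 74% | 78–88% |
| 0.9/0.5/0.5 | 78% | 93%* |

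*Run at one setting of the between-visit correlations only. The pooled range of 52–88% covers the seven sets for which those correlations were varied.

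**Other results, one round.**
- The full order is right in 39% of samples for 0.8/0.7/0.6, 31% for 0.7/0.6/0.5 and 62% for 0.9/0.7/0.5.
- The truly worst measure ranks first in about 12%, 17% and 2% for the same three sets.
- For the first two sets the sampling SD of the best-minus-worst loading difference is 0.20 and 0.26 among admissible solutions, and 0.24 to 0.32 in a second calculation, against a true gap of 0.20. For 0.9/0.7/0.5 it is 0.18 against a gap of 0.40.
- Between 19% and 39% of samples give an inadmissible solution (a loading above 1, or correlations not all positive) for these three sets and 0.8/0.6/0.4.
- Ranking the best measure first about 80% of the time from one round would take about 150 families for 0.8/0.7/0.6 and about 300 for 0.7/0.6/0.5.

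Plaque is not measured where a child is allergic to the colouring or a parent refuses it, so complete sets of three may number fewer than 30.

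**The case against.** The strongest reply is that the loadings do not decide the matter. The same section says that the choice combines quantitative and qualitative evidence and is pragmatic. That stands, and it limits the harm. It also means that the Conclusions, which speak of the most appropriate measure or measures, are not promising to find the highest loading. A reader might infer that the percentages above are the probability that the study recommends the wrong measure; the article does not support that. What remains is that the loadings are the named quantitative input and carry no indication of whether they separate the measures.

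A second reply is that an article condenses its plan, and intervals may sit in an analysis plan that is not shown. For the missing interval alone, that is fair. But an analysis plan cannot make 30 families resolve a close order, and it does not alter the article's published statements about ranking and identification.

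A third reply is that this is an early-phase study, where a sample size not aimed at ranking is normal. That is accepted; no larger sample is asked for.

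Two stronger readings should be resisted. One is that the order is close to chance. The calculations show it is clearly better than 33%, and with well-separated loadings the truly worst measure seldom ranks first. The other is that three rounds will yield three conflicting orders. The text does not say that the measurement model is fitted separately by round, and the model figures are not shown.

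**Conclusion.** The point holds as a matter of unacknowledged imprecision. The stated rule turns three loadings from 30 families into a ranking with no allowance for sampling error, and the Conclusions lack the caveat given to the ICC. Under assumed loadings, the best measure ranks first in roughly 44–78% of samples from one round and roughly 52–88% with three rounds pooled. For sets with a true best-to-worst gap of 0.20, the one-round sampling SD of that difference, about 0.2–0.3, is comparable to the gap or larger. The order is therefore informative but often unresolved. These figures depend on loadings and between-visit correlations that the article does not give, and on a correct one-factor model with independent families. Widely separated loadings would make the ranking considerably safer. The matter should be corrected, but it does not undermine the study, because the final choice also rests on other evidence.

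**What to change.** In the parents' Data analysis section, report each standardised loading and each pairwise difference in loadings with a 95% bootstrap interval. Resample whole families and keep each family's rounds together. State how inadmissible fits in the resamples are handled. Add that measures whose difference interval includes zero are treated as not separated by the quantitative evidence, so that the choice between them rests on the other evidence already named there.

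In the Conclusions, replace the claim of identification with wording such as *will give a preliminary comparison to inform the choice of*, and add an imprecision caveat like the one already written for the ICC.

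No new data or participants are needed. The cost is a short extra analysis, a few sentences and a less favourable stated conclusion.
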